### Intervention

The intervention sessions will take place at Baycrest in Toronto, at the IUGM in Montreal, or in community centers in both cities.

#### ENGAGE-MUSIC/SPANISH

ENGAGE-MUSIC/SPANISH is a 24-session program that combines leisure activities (music lessons or Spanish language lessons, and carefully selected videogames) and formal cognitive training. This intervention dose should be sufficient to show an effect based on prior studies using cognitive training similar to the one included here [10, 36, 37] or leisure-based intervention [38]. Each session will last approximately 2 h for a total of 48 training hours (see detailed schedule in Table 1). The content of the intervention was developed by a multidisciplinary team composed of neuroscientists, neuropsychologists, occupational therapists, speech therapists, and medical doctors specializing in gerontology and psychiatry. The training will be delivered in a group format of 5 to 9 participants. There will be 17 h devoted to cognitive training and 31 h to leisure activities. The program will be delivered over 16 weeks with two sessions per week during the first 8 weeks and one weekly session during the following 8 weeks. Training will be supplemented by homework (about 2 h per week). There are no criteria suggesting that the intervention should be discontinued or modified for a participant.

**Table 1 Tab1:** The ENGAGE-MUSIC/SPANISH program: class and home sessions

Week	First class of the week		Homework	Second class of the week		Homework
	Hour 1	Hour 2		Hour 1	Hour 2	
1	**Educational-1: What are attention and memory and how they are affected by age?**		Formal (60 min)	**Educational-2: Lifestyle factors influencing cognition**		Formal (60 min)
2	**Attention-1: Priority strategy**	Videogames (priority strategy): Neuropeak	Formal (30 min) + Neuropeak (30 min)	**Attention-2: Priority strategy**	Videogames (priority strategy): Tap to Cook	Formal (30 min) + Tap to Cook (30 min)
3	**Attention-3: Priority strategy**	Videogames (priority strategy): Neuropeak + Tap to Cook	Formal (30 min) + Neuropeak (30 min)	**Attention-4: Priority strategy**	Videogames (priority strategy): Neuropeak + Tap to Cook	Formal (30 min) + Tap to Cook (30 min)
4	**Memory-1: Introduction of all strategies + see it and say it + habits + memory aids**		Formal (30 min) + Neuropeak (30 min)	Music or Spanish-1 (see it and say it)		Music/Spanish (30 min) + Tap to Cook (30 min)
5	**Memory-2: Spaced retrieval**	Music or Spanish-2 (spaced retrieval)	Formal (30 min) + Neuropeak (30 min)	Music or Spanish-3 (spaced retrieval)		Music/Spanish (30 min) + Tap to Cook (30 min)
6	**Memory-3: Make it meaningful and mental imagery**	Music or Spanish-4 (make it meaningful)	Formal (30 min) + Neuropeak (15 min) + Chicken Run (15 min)	Music or Spanish-5 (mental imagery)		Music/Spanish (30 min) + Tap to Cook (30 min)
7	**Memory-4: Face-name association**	Music or Spanish-6 (face-name association)	Formal (30 min) + Neuropeak (15 min) + Chicken Run (15 min)	Music or Spanish-7 (face-name association)		Music/Spanish (30 min) + Tap to Cook (30 min)
8	**Memory-5: Method of Loci**	Music or Spanish-8 (method of Loci)	Formal (30 min) + Neuropeak (15 min) + Chicken Run (15 min)	Music or Spanish-9 (method of Loci)		Music/Spanish (30 min) + Tap to Cook (30 min)
9	**Memory-6: Review all strategies**	Music or Spanish-10 (see it and say it)	Formal (30 min) + Music/Spanish (30 min) + Tap to Cook (30 min) + Neuropeak (15 min) + Chicken Run (15 min)			
10	Music or Spanish-11 (spaced retrieval)		Music/Spanish (60 min) + Tap to Cook (30 min) + Neuropeak (15 min) + Chicken Run (15 min)			
11	**Memory-7: Review/scenarios**	Music or Spanish-12 (make it meaningful)	Formal (30 min) + Music/Spanish (30 min) + Tap to Cook (30 min) + Neuropeak (15 min) + Chicken Run (15 min)			
12	Music or Spanish-13 (mental imagery)		Music/Spanish (60 min) + Tap to Cook (30 min) + Neuropeak (15 min) + Chicken Run (15 min)			
13	Music or Spanish-14 (face-name association)		Music/Spanish (60 min) + Tap to Cook (30 min) + Neuropeak (15 min) + Chicken Run (15 min)			
14	Music or Spanish-15 (method of Loci)		Music/Spanish (60 min) + Tap to Cook (30 min) + Neuropeak (15 min) + Chicken Run (15 min)			
15	Music or Spanish-16 (free use of strategy)		Music/Spanish (60 min) + Tap to Cook (30 min) + Neuropeak (15 min) + Chicken Run (15 min)			
16	**General review**	Music or Spanish-17 (free use of strategy)	Not applicable			

Bold typeface corresponds to formal cognitive training. Trained memory and attention strategies are in parentheses

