### Randomization and blinding procedure

The opportunity to exclude either music or Spanish training will be offered to all participants prior to randomization. Randomization will be done individually (i.e., one participant at a time as they enter the study) with random lists of binary numbers. Lists will be generated using the Random.org online software. Randomization will be controlled by a person from the Montreal site who is independent of the study. A first randomization will allocate participants to the intervention or control condition by matching the sequential list of participant identification codes with the list of random condition allocation. This will be done with a 2 to 1 ratio between intervention and control conditions. A second randomization will be used to allocate participants in the intervention condition to either Spanish or music training, using a 1 to 1 ratio for participants who did not exclude either of these two activities. Participants randomized in the intervention condition who excluded music or Spanish training will be placed in their preferred activity. Recruiting staff will contact (via telephone) the trial allocation office in charge of randomization once a participant has consented to participate and will be given the allocation. The allocation and sequence of allocation will be concealed from evaluators.

Evaluators who will be assessing the participants will be blinded to the hypotheses and to the group assignment of participants. Participants will be asked not to mention their group assignment to evaluators. Any breach of this group assignment blinding by participants will be noted, but since evaluators will be blinded from the hypotheses this should have minimal effect on integrity. Activity leaders will not be blinded to the study hypotheses. Although participants will know that they are in the Spanish, music, or documentary discussion group, they will not be informed of the study hypotheses, i.e., participants assigned to ENGAGE-DISCOVERY will be unaware that it is an active control condition. To keep participants blinded from the hypotheses and reduce the likelihood that the expectations of participants bias the data [29], close attention will be paid to ensure that the content of the intervention and the wording of recruitment documents and consent forms do not convey the expectations that one condition is inferior in terms of its effect on the brain and cognition.

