#### ENGAGE-DISCOVERY

The ENGAGE-DISCOVERY program (Table 2) will be used as an active control. This will be structured in the same manner as the ENGAGE-MUSIC/SPANISH program and will comprise the same number of classes, hours of homework, and ratio of formal classes to leisure activities. The content of the ENGAGE-DISCOVERY program was selected to be less cognitively stimulating than the intervention, yet interesting and enjoyable, to ensure the same level of expectation and participation.

**Table 2 Tab2:** The ENGAGE-DISCOVERY program: class and home sessions

Week	First class of the week		Homework	Second class of the week		Homework
	Hour 1	Hour 2		Hour 1	Hour 2	
1	**Educational-1: Myths and reality about aging; discover your brain**		Formal (60 min)	**Educational-2: Attention and working memory**		Formal (60 min)
2	**Educational-3: Semantic memory**	Videogames: Freecell	Formal (30 min) + Freecell (30 min)	**Educational-4: Episodic memory**	Videogames: Words	Formal (30 min) + Words (30 min)
3	**Educational-5: Memory and senses**	Videogames: Freecell + Words	Formal (30 min) + Freecell (30 min)	**Educational-6: Procedural memory**	Videogames: Freecell + Words	Formal (30 min) + Words (30 min)
4	**Educational-7: Executive functions**		Formal (30 min) + Freecell (30 min)	Documentary and discussion		Reading (30 min) + Words (30 min)
5	**Educational-8: Neuroplasticity**	Documentary and discussion	Formal (30 min) + Freecell (30 min)	Documentary and discussion		Reading (30 min) + Words (30 min)
6	**Educational-9: Nutrition and exercise**	Documentary and discussion	Formal (30 min) + Freecell (15 min) + Equilibrium (15 min)	Documentary and discussion		Reading (30 min) + Words (30 min)
7	**Educational-10: Sleep and stress management**	Documentary and discussion	Formal (30 min) + Freecell (15 min) +Equilibrium (15 min)	Documentary and discussion		Reading (30 min) + Words (30 min)
8	**Educational-11: Health and mood**	Documentary and discussion	Formal (30 min) + Freecell (15 min) + Equilibrium (15 min)	Documentary and discussion		Reading (30 min) + Words (30 min)
9	**Educational-12: Review—different types of memory**	Documentary and discussion	Formal (30 min) + Reading (30 min) + Words (30 min) + (15 min) + Equilibrium (15 min)			
10	Documentary and discussion		Reading (60 min) +Words (30 min) + Freecell (15 min) + Equilibrium (15 min)			

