### Adherence to treatment and retention

A number of strategies will be used to reduce attrition and promote retention over the 24-month follow-up. The coordinator of the study will be available by phone to discuss potential problems. In case of reduced adherence, we will contact the participant or his/her informant to identify the reasons and/or barriers that reduce their attendance and help identify solutions. The choice of a preference trial where participants are given the possibility to exclude an activity they dislike was also made to increase adherence to treatment. The team will remain in contact with the participants during the long-term follow-up through yearly telephone calls and greeting cards for the festive season. The attrition rate is expected to be approximately 18% based on our most recent study which used a similar program [10]. The characteristics of those who withdraw will be analyzed and intent-to-treat analyses will be used. Participants who withdraw from the program will be invited to come for follow-up assessments.

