### Statistical analyses

#### Sample size

The trial will recruit 144 participants. The sample size was estimated from a power analysis with G*power based on pilot findings collected with the MEMO program [10, 12], using word recall and face-name associations tasks. The MEMO program is included as part of the formal training in this intervention in addition to stimulating leisure activities and attentional training. Therefore, it is reasonable to expect that the effect should be at least as large as the one observed when using MEMO alone. The pilot data indicated a medium effect size for the group-by-time interaction when examining face-name association and a large effect size when examining word recall (see Additional file 2: Appendix 2). It shows that the sample size would be sufficient to detect an interaction given a similar effect size considering the same attrition rate that we obtained in this prior study (18%). Half of the sample will be recruited in Montreal and the other half will be recruited in Toronto.

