#### Analysis of efficacy and maintenance on primary and secondary outcomes

Descriptive statistics will be used for demographics and baseline characteristics, with means and standard deviations given. We will compare the intervention groups on these variables using one-way analysis of variance (ANOVA) for continuous variables and Chi-square analyses for discrete variables. The primary efficacy analysis will be done with a modified intention-to-treat approach retaining all participants and identifying the characteristics of participants withdrawing from follow-up as well as the causes for withdrawal. As proposed for preference trials, a first set of analyses will only use fully randomized participants. This will be followed by analyses of the comprehensive cohort which will include those in the preference arms.

The linear mixed model will be used to assess the efficacy of the intervention. The mixed linear model has many advantages over typical ANOVA; it handles correlated data and is robust to unbalanced design, hence allowing for the inclusion of all participants, including those missing at follow-up. Missing data will not be imputed as mixed models use all available data, including those from participants having incomplete follow-up. The fixed effects will be intervention (ENGAGE SPANISH/MUSIC versus ENGAGE DISCOVERY), time (PRE versus F4), and their interaction. A significant interaction is expected if the intervention is more beneficial than the control condition. When an interaction is found, we will look at whether there is a significant difference between PRE and F4 in each group and assess group differences on change scores at post-training ([PRE – F4]/|PRE|). Efficacy is supported if the F4 change score is larger in the intervention group than in the control group. All analyses will be adjusted for site and baseline performance.

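### Training is given in small classes nested in arm, yet the stated efficacy model, sample-size text and chi-square test contain no class-level term

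*Protocol article*

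**What the plan says.** Allocation is by person. The section on randomization and blinding states "Randomization will be done individually", and on the split between intervention and control, "This will be done with a 2 to 1 ratio between intervention and control conditions".

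Delivery is by class. For ENGAGE-MUSIC/SPANISH: "The training will be delivered in a group format of 5 to 9 participants", over 24 two-hour sessions. For ENGAGE-DISCOVERY: "This will be structured in the same manner as the ENGAGE-MUSIC/SPANISH program and will comprise the same number of classes". The control class size is not restated. Interaction between classmates is intended in both arms: choral singing and role play in the intervention, and a debate after each documentary in the control.

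The section on quality control and monitoring puts one leader per city in charge of the cognitive sessions and the control programme. Separate professional teachers give music and Spanish.

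The primary model is described so: "The fixed effects will be intervention (ENGAGE SPANISH/MUSIC versus ENGAGE DISCOVERY), time (PRE versus F4), and their interaction". Site and baseline performance are added as adjustments. The text remarks that mixed models cope with correlated data but does not name the source of correlation, and it describes no random effects. The Jessen questions are compared between conditions by chi-square.

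On size: "The trial will recruit 144 participants", from a G*Power calculation on pilot data that allows for attrition. Clustering is not mentioned.

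**The concern.** People who share a class, its discussions and (for music and Spanish) its teacher for four months may gain more alike than people in different classes. Because every class sits wholly within one arm, any between-class variation in gain goes straight into the arm contrast. A model that carries only person-level error does not count that variation.

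The point estimate is not shown to be biased; what is at stake is its precision. A nominal p below 0.05 on the memory composite would be weaker evidence than it appears. The same applies to the non-imaging secondary outcomes and to the exploratory comparison of music with Spanish. If the analysis does allow for class, the cost appears as power instead, and the sample-size text makes no provision for that.

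**Working it through.** **The plan's own figure.** The total of 144 can be neither confirmed nor refuted. The article gives no target power and describes the pilot effects only as medium and large; the details are in Additional file 2, Appendix 2, which is not shown.

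**Inputs from the protocol**
- Total 144, allocated 2:1, so 96 and 48.
- Attrition: "The attrition rate is expected to be approximately 18" per cent, so 144 × 0.82 ≈ 118 completers (about 79 and 39).
- Class size 5 to 9, midpoint 7. This is stated for the intervention and inferred for the control.
- Two-sided test at 0.05.

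**Assumed:** class ICC of the adjusted gain from 0 to 0.10, equal class sizes, the same ICC in both arms, and a normal approximation.

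**Number of classes at 7 per class:** 144/7 ≈ 21, of which 96/7 ≈ 14 are intervention and 48/7 ≈ 7 control. At 9 or 5 per class the total is 16 or about 29.

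**Completers per class:** m = 7 × 0.82 = 5.74.

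**Formulas**
- Design effect DE = 1 + (m − 1) × ICC
- True SE ÷ SE that ignores class = √DE
- Actual type I error = 2 × [1 − Φ(1.96/√DE)]
- Effective number of completers = 118/DE

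| ICC | DE | √DE | Type I error | Effective completers |
|---|---|---|---|---|
| 0 | 1.00 | 1.00 | 5.0% | 118 |
| 0.01 | 1.05 | 1.02 | 5.5% | 113 |
| 0.02 | 1.09 | 1.05 | 6.1% | 108 |
| 0.05 | 1.24 | 1.11 | 7.8% | 95 |
| 0.10 | 1.47 | 1.21 | 10.65% | 80 |

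Worked row, ICC 0.05: DE = 1 + 4.74 × 0.05 = 1.237; √1.237 = 1.112; 1.96/1.112 = 1.762; two-sided tail 0.078.

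**Sensitivity to class size at ICC 0.05:** starting sizes of 5 and 9 leave 4.10 and 7.38 completers. DE is then 1.155 and 1.319, and the type I error 6.8% and 8.8%.

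**Degrees of freedom.** With 21 classes in two arms, a class-level comparison has about 19 degrees of freedom (critical t 2.09). At person level there are about 116 (critical t 1.98). The normal approximation above leaves out this further, smaller penalty.

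**The case against.** The strongest objection is that independence is read out of silence. The article lists fixed effects and covariates and describes no random effects, not even one for the participant. A condensed article may leave that structure to a full protocol or analysis plan. A reader might infer that the trial's model does treat participants as independent and that its intervals are too narrow as a matter of fact. The documents do not support that: they never say so, and at an ICC of zero nothing is lost. This limits the point to a conditional one but does not remove it. The remark about correlated data is tied in its context to unbalanced data and incomplete follow-up. The chi-square test is also specified outright and has no place for a class effect, and a random effect added later would not change the planned 144.

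A second objection is that several features limit clustering. The programmes are manualised and monitored, part of the training is individual (tablet games, homework), and one leader per city serves both arms. A leader's influence common to both arms should largely cancel from the contrast, and baseline adjustment means that the relevant ICC is that of the adjusted gain. These are good reasons to expect a modest ICC. Site adjustment is weaker protection than it looks: a site main effect moves baseline and follow-up together and does not absorb class differences in gain. Peer effects remain, as do effects of music and Spanish teachers, who exist only in the intervention arm.

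A third concerns size and reach. Using 7 analysed per class would give a type I error of 12.1% at ICC 0.10, but that ignores the protocol's own 18% attrition. A reader might also extend the result to every secondary outcome. That does not follow: imaging covers a subgroup of 54, so these class sizes do not carry over. Functional MRI has its own group-level analysis, and the Jessen outcome is not in a mixed model at all.

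**Conclusion.** The point holds in conditional form. Classes are nested in arm by design, and neither the stated model terms, the sample-size text nor the chi-square test has a place for them. Run as written, the analysis understates the standard error whenever gains correlate positively within class. On the inputs above, the type I error runs from 5% at ICC 0 to about 10.7% at ICC 0.10, with about 8% at ICC 0.05. Below an ICC of about 0.02 the effect is slight.

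These figures rest on an assumed ICC range, on equal class sizes and on an inferred control class size. The first analysis set, restricted to fully randomised participants, could have fewer people per class and so a smaller design effect. The change is worth making before the efficacy analysis; the documents do not show that the efficacy inference is invalid.

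**What to change.** - Record a class identifier for every participant.
- Add a class random effect acting on the post-baseline visits (F4, F24) to the mixed models for the primary outcome, the non-imaging secondary outcomes and the exploratory comparison of music with Spanish. Use Satterthwaite or Kenward-Roger degrees of freedom.
- For the Jessen outcome, replace the chi-square test with a class-adjusted method, such as a mixed logistic model or GEE with a small-sample correction.
- Report the estimated class ICC, and say in the sample-size text how power changes over a stated ICC range.
- If the full analysis plan already contains a class effect, confirm it and bring the chi-square test into line.

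The cost is one additional variable and one model term, with slightly wider intervals and fewer degrees of freedom. With about 21 classes, only about 7 of them control, the class variance will be imprecise and may be estimated at zero. The plan should therefore state in advance what will be reported in that case.

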##### Formal cognitive training

Cognitive training sessions will comprise 4 h of psychoeducation on cognitive aging, 4 h of attentional training, 8 h of memory training, and 1 h for general review. Psychoeducation sessions will include courses about the brain and how aging affects memory and attention, as well as tips for a healthier lifestyle to promote successful aging (sleep, diet, cognitive engagement, physical activity, social life, depression and stress management, etc. [12, 39]). Training for attention and memory will focus on strategies that were found to improve cognition in older adults. The attention training component relies on computerized exercises taken from Gagnon and Belleville [40] and Bherer et al. [41]. In these exercises, participants practice attentional control in dual-task situations by varying the amount of attention they allocate to one task over the other (priority strategy; e.g., allocate 80% of one’s attention to task A and only 20% to task B) in different blocks of practice. Participants will receive feedback on their performance to increase awareness of their ability to control their attention. The “memory” component of the program is taken from the MEMO program [10, 12] and from the Memory and Aging Program [39, 42]. Participants learn how to maximize their memory performance by using internal and external strategies. Internal strategies will include: learning how to visualize and/or formulate an intention out loud to maximize the chances of remembering it later (“see it and say it”); learning “spaced retrieval”, which is a strategy that consists of progressively increasing the delay between retrieval trials to strengthen encoding of new information; learning how to create semantic connections between new information and existing knowledge; and learning “mental imagery” by creating mental images that associate two elements that need to be memorized in tandem. Mental imagery will be more specifically used to remember a person’s face and name, and to remember lists (method of loci). External strategies will include the use of memory aids (e.g., agenda, to-do lists) and ways to organize the environment in a manner that facilitates memory (e.g., creating routines).

